#### Drug information and education service

The practice pharmacist will provide a drug information service for practice staff. Queries can be made to the pharmacist in person, by telephone or via email. All queries (and responses) will be documented by the pharmacist. Practice staff will also be invited to attend pharmacist-led group education sessions targeting topics relevant to them (e.g. new therapy or treatment protocols), and a weekly drug information newsletter may also be produced by the pharmacist and provided to staff.

#### Quality assurance activities

The practice pharmacists will undertake a Drug Use and Evaluation (DUE) program in the clinic. The pharmacists will review current prescribing patterns, evaluate these against current best practice guidelines, and implement an intervention to address deficiencies identified using established DUE methodology [20]. A pharmacotherapeutic area of concern or importance will be identified by the pharmacist in conjunction with the GPs and clinic staff. The practice team, with assistance from the research team, will decide upon audit criteria and measurement instruments will be derived from published clinical practice guidelines. The pharmacist will collect and evaluate data relevant to medication use in this area by retrospectively reviewing electronic medical records. Confidentiality of data will be ensured by de-identifying all information collected. Results and feedback will be provided to staff. Multifaceted strategies to improve the quality of prescribing in the selected area will be developed and implemented by the interdisciplinary team, and re-evaluated at the end of the study period. Patients will not be recruited or consented to this part of the study, and no identifying data will be collected.

#### Monitoring and follow up

Actions arising from the DUE program (e.g. development and implementation of clinical guidelines, criteria, treatment protocols, education programs) will be assessed for effectiveness after six months by repeating the prescribing audit to complete the DUE cycle [20].

### Outcomes

#### Outcomes of long patient consultations

##### Medication-related problems

The primary outcome of the long consultations will be the number of MRPs identified by practice pharmacists and the number of identified MRPs that are resolved as a result of the pharmacists’ interventions. The number of MRPs, number of recommendations made by the pharmacists and the number of recommendations accepted/implemented will be recorded and determined by chart audit and/or patient interview, conducted by a research assistant. The types of problems will be categorized by the research team according to the criteria described by Strand et al [21]. The severity of the MRPs and the likely consequences if they had not been addressed will be assessed by an expert panel using a risk classification system [22].

### Other outcomes

#### Satisfaction

Patient satisfaction with the practice pharmacist will be determined by a structured, satisfaction questionnaire adapted from a previously validated patient satisfaction survey by Baker regarding physician consultations [24,25]. The questionnaire will be anonymous and provided at the end of any interaction with the pharmacist (including long patient consultations and short patient consultations). Participants will be requested to complete and return the questionnaire before they leave the practice or at their earliest convenience, using a reply-paid envelope.

#### Quality of prescribing and medication use

The effectiveness of the DUE program will be assessed by re-evaluating medication use in the targeted population at the end of the study and comparing this to baseline data.

#### Drug information queries

The number of drug information queries made and answered, the type of queries made and by whom, will be evaluated at six months.

#### Short patient consultations

General information regarding the nature of the short consultations will be recorded, including the reason for referral, type of service provided and average time spent.

#### Experiences and feedback

The views of a sample of stakeholders on their experiences with this new service will be explored using interviews and/or focus groups at the study’s conclusion. Patients and staff will have the opportunity to share their thoughts on the perceived benefits and challenges of the service and how it could be improved and developed further.

### Data analysis

Data will be entered into the Statistical Package for Social Sciences (SPSS) for Windows Version 19.0 (IBM, New York, USA) and analyzed using standard descriptive methods. Bivariate analysis will be performed between pre- and post-intervention data, using paired t-tests for continuous variables, McNemar chi-square tests for categorical variables, and Wilcoxon matched-pairs signed-ranks tests for ordinal variables. Comparisons between practices may be done using repeated measures analysis of variance (ANOVA). Binary logistic regression may be performed to identify independent predictors of having medication-related problems and effects on adherence and other outcomes.

Qualitative data management will be facilitated using NVivo® (Version 9, Qualitative Solutions & Research International, Melbourne, Vic). Interview transcripts will be read by two independent researchers and coded for emergent themes. Any discrepancies will be discussed and sorted in team meetings in the presence of a third researcher. A framework approach may be utilized whereby a thematic framework, based on *a priori* issues, will be applied to the data [26]. This will allow data to be easily indexed and charted, thus aiding subsequent interpretation.

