#### Baseline data collection

Baseline data will be collected by the research assistant using a structured questionnaire, either in person (at the clinic or the person’s home) or by telephone, and will include demographic information (age, sex, ethnicity, education, socioeconomic status, living arrangements etc.), health information (general health, health service use, health literacy [15] etc.), and medicines information (medication risk [14] adherence [16,17] etc.). The research assistant will then organize for the participant to meet the practice pharmacist for a long consultation.

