#### Monitoring and follow up

Participants will be followed up by the research assistant at three and six months either in the clinic or by telephone to collect data about implementation of pharmacist recommendations, resolution of MRPs identified by the practice pharmacist, participant’s medication adherence and participant’s general health and wellbeing.

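### Adherence and general health are recorded at three visits with 25% loss expected, but the planned pre-post tests use only complete two-visit pairs and leave the post visit undefined

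*Protocol article*

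**What the plan says.** **Schedule.** The Baseline data collection section lists "medicines information (medication risk [14] adherence [16,17] etc" and, under health, "health information (general health, health service use, health literacy [15] etc". The Monitoring and follow up section for long consultations says "Participants will be followed up by the research assistant at three and six months", and the items collected then include "participant’s medication adherence and participant’s general health and wellbeing". Adherence and general health are therefore recorded on three occasions. Wellbeing is named only at follow-up.

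**Expected loss.** The Sample size section needs 37 participants for medication-related problems (MRPs) and recruits at least 50, allowing for 25% loss.

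**Analysis.** The Data analysis section commits to the following: "Bivariate analysis will be performed between pre- and post-intervention data, using paired t-tests for continuous variables, McNemar chi-square tests for categorical variables", with "Wilcoxon matched-pairs signed-ranks tests for ordinal variables". It does not say which follow-up visit counts as post-intervention. Repeated measures ANOVA appears as an option, but only for comparing the two practices. A further optional sentence reads: "Binary logistic regression may be performed to identify independent predictors of having medication-related problems and effects on adherence and other outcomes".

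**The concern.** The Abstract names adherence as an outcome measure. Each committed test compares two occasions, so with three visits there are two possible post values and the plan does not choose between them. As named, the tests also need both members of the pair. A participant seen at baseline and 3 months but lost by 6 months adds nothing to the 6-month result. On the plan's own allowance that could apply to up to 13 of 50 participants (50 - 37).

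Two things are at stake. One is a little precision. The other is robustness: if those who leave differ in adherence from those who stay, a complete-pair comparison can be biased where an analysis of all visits would not be. The logistic sentence does not fill the gap. It is a natural tool for finding predictors of a yes/no status. In a cohort where everyone receives the consultation, it does not by itself estimate the average change from before to after.

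**Working it through.** **1. The plan's own figures.** Paired t-test, mean change 1, SD 2.1, two-sided 0.05: power is 79.3% at n = 36 and 80.5% at n = 37, so 37 is right. Then 37/(1 - 0.25) = 49.3, so 50. Both figures reproduce. They concern MRPs; the article gives no SD, effect or correlation for adherence.

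**2. Assumptions for what follows.** Scores have SD 1 at each visit, 50 participants are enrolled and 37 are seen at 6 months. The between-visit correlation r is taken as 0.3, 0.5 or 0.7. The 0.5 is the plan's value for MRPs, borrowed here.

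**3. Precision of the 6-month change.**
- Complete pairs: variance = 2(1 - r)/37.
- Likelihood model on all visits, when none of the 13 lost were seen at 3 months: variance = (1 - r²)/37 + (1 - r)²/50.
- At r = 0.5: 1/37 = 0.02703 against 0.75/37 + 0.25/50 = 0.02027 + 0.00500 = 0.02527. The ratio is 0.935, and the standard errors are 0.164 and 0.159 SD.

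| r | none of the 13 seen at 3 months | 6 seen | all 13 seen |
|---|---|---|---|
| 0.3 | 0.909 | 0.904 | 0.900 |
| 0.5 | 0.935 | 0.923 | 0.913 |
| 0.7 | 0.961 | 0.941 | 0.924 |

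Entries are the variance of the all-visit model divided by that of complete pairs. The complete-pair variance is thus higher by 1/0.961 = 1.04 to 1/0.900 = 1.11 times. Simulation with estimated covariances and drop-out related to adherence widens this to about 3-12%, and in some settings the gain disappears.

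**4. Bias if later drop-out depends on baseline adherence.** Half of the 25% is assumed lost at random before 3 months, the rest later. Given the baseline score, the expected change falls by (1 - r) per SD of baseline. If completers' baseline mean is s SD above that of all enrolled, the bias of the complete-pair change is -(1 - r)s. At r = 0.5:
- s = 0.12 gives -0.06 SD;
- s = 0.18 gives -0.09 SD;
- the limit, where the later loss takes exactly the lowest 12.5/87.5 = 1/7 of those remaining, has s = 0.2257/0.8571 = 0.263 and gives -0.13 SD;
- weak dependence, s = 0.06, gives -0.03 SD.

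On an assumed true change of 0.3 SD, 0.06-0.09 SD is an understatement of 20-30% (0.06/0.3 and 0.09/0.3). The sign reverses if the more adherent leave.

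**5. Bias if later drop-out depends on 3-month adherence.** The bias is (r between 3 and 6 months minus r between baseline and 3 months) × s, with s now the shift in completers' 3-month mean. Equal correlations give 0. With 0.7 and 0.5, and s = 0.18, it is 0.2 × 0.18 = 0.036, about 0.04 SD.

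Under the drop-out in steps 4 and 5, which depends only on recorded values, a correctly specified likelihood model over all visits is unbiased up to simulation error.

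**6. A different target.** If the average of the two follow-ups were wanted, its change from baseline has variance 1.5(1 - r) per participant against 2(1 - r), a ratio of 0.75. That answers a different question from the 6-month change and is not the size claimed here.

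**The case against.** The strongest reply is that nothing here is invalid. The committed tests are all paired, suit a small two-clinic before-after study, and apply to adherence as to any other variable. Adherence is not the primary outcome. Choice of visit, longitudinal modelling and missing-data handling are often left to a full protocol or analysis plan, which is not shown. The bias figures rest on an assumed strength of drop-out that the article does not give. All of this stands, and it limits the point to an improvement.

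Three stronger readings are tempting and should be resisted.

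- A reader might infer that pairing and the measurement scale are thrown away. They are not. All three tests keep the pairing, and the t-test and Wilcoxon test keep a continuous or ordinal score.
- A reader might infer that logistic regression is the adherence analysis and would be fitted to stacked before and after records with wrong standard errors. The sentence is optional and reads most naturally as a search for predictors. No stacking is stated, and one record per person would not break the pairing. Nor is it shown that adherence will be reduced to yes/no: the adherence instruments appear only in the abbreviation list, and their scoring is not described.
- A reader might infer that the 3-month data are discarded. Paired tests could be run at each visit, since the article does not restrict the post visit.

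What the reply does not remove is that the text commits to two-occasion tests without fixing the occasion, and that the one repeated-measures method it names is confined to comparing practices.

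**Conclusion.** The point holds as a modest improvement to the analysis of a non-primary outcome. As named, the tests for adherence and general health use complete pairs only, the post visit is not fixed, and no named analysis takes all three visits for the overall change. The cost is about 3-12% extra variance for the 6-month change. A bias of 0.06-0.09 SD arises only under an assumed strong dependence of drop-out on baseline adherence, and is judged against an assumed 0.3 SD change. It is between about zero and 0.04 SD if drop-out depends on the 3-month value. For scale, the standard error of the complete-pair change is about 0.16 SD at a correlation of 0.5. The MRP outcome and its sample size are not affected by this point.

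**What to change.** For adherence and general health, state that the main estimate is the 6-month minus baseline change, from one longitudinal model fitted to all available visits. Use a linear mixed model for a score, or GEE or a mixed logistic model for a yes/no status. Enter visit as a three-level factor and clinic as a fixed term, and allow for correlation within participant. Report the 6-month change with its 95% interval and the 3-month change beside it. Keep the paired tests as supporting analyses, naming the visit each one uses. Reword the logistic sentence so that it covers predictors only and not the pre-post effect.

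The cost is a change of analysis wording and slightly more modelling work. No new data are needed, and the models can be fitted in the named software. The downside is reliance on a missing-at-random assumption, which should be stated; ordinary GEE needs the stronger condition that loss is unrelated to earlier responses, unless it is weighted.

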### Ethics

This study has been approved by the Monash University Human Research Ethics Committee.

## Discussion

To the best of our knowledge, this is the first study in Australia to evaluate an interdisciplinary, multifaceted practice pharmacist role to improve the quality use of medicines by both patients and clinic staff. The comprehensive nature of this intervention aims to optimise medicine use at several levels. Although the study will be conducted with a pre-post design, subjects will serve as their own controls, thus eliminating inter-subject variability and reducing confounding. Additionally, the study will be conducted in more than one primary care clinic allowing for inter-practice comparison and improving external validity.

The study involves mixed methods to capture and measure a variety of data to explain the impact of the intervention. Additionally, a range of process, health, medication management and humanistic outcomes will be collected. By using both quantitative and qualitative methods, a deeper exploration of the intervention can occur. This will enable a more comprehensive exploration of the various intricacies involved in both types of settings, thus allowing identification of the optimal models of pharmacist integration for various primary care clinics.

### Limitations

The before and after design, which lacks a concurrent control group, may compromise the internal validity of the study and limit the conclusions drawn from the results. Non-random sampling means external validity is also compromised. However, this design is the most suitable and practical given the nature of the intervention; a controlled trial with randomization at the level of the patient would be severely limited by contamination, and a cluster randomized controlled trial would require multiple practices, which is not feasible in the context of limited resources.

## Conclusion

The integration and co-location of a practice pharmacist into Australian primary healthcare clinics is uncommon and has not been evaluated. This study will implement and evaluate a new collaborative pharmacist role and assess its effects on optimizing medication outcomes at various levels. The study will provide useful data to guide further research and development in this area.

## Abbreviations

MRP: Medication-related Problem; GP: General Practitioner; HMR: Home Medicines Review; DUE: Drug Use Evaluation; TABS: Tool for Adherence Behaviour Screening; BBQ: Beliefs and Behaviour Questionnaire.
